### Statistical methods

#### Primary analysis

The main analysis examining the primary outcome (proportion of guideline concordance) will be intention to treat using multilevel regression models (linear or Poisson regression, as appropriate), with time-point and intervention status as fixed effects. Clusters will be examined as a random effect for inclusion into the model. Covariates will include the stratification factors, which are state, clinic size (GP equivalent full time >5 (yes/no)), and location (urban vs regional/rural).

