### Sample size

A sample size of 86 clinics (clusters), with a minimum of one GP per cluster and assuming a GP dropout rate of 25%, has >80% power to detect a medium-large effect size of Cohen’s d of 0.69 (assuming a GP-level outcome score change of 1.2 on a scale with score range of 0 to 9 and a standard deviation of 1.75 as identified in a pilot study of the primary outcome tool; correlation between baseline and follow-up measurements of 0.3, and two-sided significance of 0.05).

We estimate that each GP cluster will recruit a minimum of 7 and a maximum of 24 patients (the cut-off to ensure that the patient sample is not skewed by a high-recruiting cluster) over the study period. Based on our analysis of high-caseload GPs [32], we estimate that there will be approximately 22 eligible patients/year/GP. Accounting for a 66% estimated rate of refusal to participate as observed in another study that recruited participants with mental health conditions in the Australian general practice setting [33], we estimate that at least 7 eligible patients will be successfully recruited by each participating GP in a 9-month period.

We anticipate that approximately 448 patients who are recruited within the 9 months (224 from control clinics and 224 test clinics; 7 per clinic/cluster) will have 3-month data. These patient numbers assume up to 25% of the 86 recruited GPs will drop out of the study. Using data from these patients, we will have 90% power to detect medium effects (Cohen’s d = 0.5) in secondary outcome measures between two groups (test/control) at 3 months. Calculations assume an alpha of 0.01, ICC of 0.03, and correlation of 0.5 between individual scores. Calculations were made using Cluster statistical software [34].

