### Outcomes

#### Primary outcome

The primary outcome is concordance with guideline recommendations by participating GPs. Guideline concordance will be assessed at baseline and 9 months later using virtual simulated patient scenarios. At each data collection point, GPs will be presented with three virtual scenarios of varying levels of complexity and patient circumstance. The three virtual scenarios for each GP at each data collection point will be randomly selected from a set of eighteen virtual scenarios, controlling for learning effects and order effects, and balancing rigorous measurement with participation burden. We based the development of these scenarios on 20 interviews with patients who have lived experiences of work-related mental health conditions to ensure that virtual scenarios reflect the range of patient characteristics that a GP would see.

This approach has been used previously to evaluate practice and as an educational tool in compensable injury research with GPs in Europe [36] and with physiotherapists in Australia [37]. The virtual scenarios are approximately 15 min duration each and focussed on typical presentations to GPs by patients with work-related mental health conditions. Each virtual scenario includes a short video of a simulated patient who describes their symptoms, circumstances and context. Participating GPs are then prompted to respond to questions about how they would assess, diagnose, and manage the patient in the virtual scenario.

Guideline-concordant responses to the scenarios will be measured using a tool that reflects the checklist of indicators that have been included in the Guideline. Responding to each set of three virtual scenarios can result in a best score of 9 or a worst score of 0. The tool was pilot tested with three groups: (1) GPs who are experts in the Guideline, (2) GPs who are not familiar with the Guideline, and (3) medical and research students who have no clinical general practice expertise. The tool was found to have a scale reliability score of Cronbach’s *α*=0.74.

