### Economic evaluation

The economic evaluation will take a societal perspective in quantifying the additional costs (savings) and health gains associated with the intervention within the trial period. The primary outcome for the economic evaluation will be GP concordance with guideline recommendations. The secondary outcome for the economic evaluation will be quality-adjusted life-years (QALYs) in participating patients; calculated based on SF-36 v2 data at each time-point [44] and using an area-under-the-curve approach.

The cost analysis will capture direct costs of the intervention and control conditions (based on project records and fidelity data), medical costs during the trial period, and productivity gains during the trial period. Medical costs will be estimated based on patient-level administrative data from the Medicare Benefits Scheme (MBS), from Pharmaceutical Benefits Scheme (PBS), and from workers’ compensation schemes (for those patients who submit a claim and provide consent for data access), plus patient self-report of health service use funded by other payers (e.g. hospitalisations and allied health care). Productivity gains will be estimated based on patient-level data regarding return to work from the National Return To Work Survey items. Results of the economic evaluation will be expressed as cost per point improvement in concordance with the Guideline, and cost per QALY gained.

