#### Secondary analysis

*Patient analyses*: Using a similar mixed model approach as in the main analyses, changes in patient health status (using the SF-36 v2), and work participation (using relevant measures of the National Return To Work Survey) will be measured by comparing the scores on patient surveys from baseline to 3, 6, and 9 months following their initial GP consultation.

*Adjusted analyses*: The main analysis and subgroup analyses above include adjustment for the stratification factors, which are state, clinic size (GP equivalent full time >5 (yes/no)), and location (urban vs regional/rural), additional mental health training.

*Missing data*: As the GP and patient-level data are longitudinal samples, a missing data analysis will be done on each longitudinal data set and investigations made for predictors of missingness. These investigations will examine the effect of key demographic and other factors particularly on the presence of missing outcomes. If outcome data is found to not be missing at random, then multiple imputation will be applied using the predictors for missingness.

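### The primary outcome is a 0–9 score when defined, sized and costed, but a proportion with a linear or Poisson model when analysed, so the primary effect measure is not fixed; the main-analysis covariate lists also differ

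*Protocol article*

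**What the plan says.** Three sections of the protocol article treat the primary outcome as a score.

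- Primary outcome: "Responding to each set of three virtual scenarios can result in a best score of 9 or a worst score of 0".
- Sample size: the calculation rests on a "GP-level outcome score change of 1.2 on a scale with score range of 0 to 9 and a standard deviation of 1.75", which the article calls a "medium-large effect size of Cohen’s d of 0.69". It assumes 86 clinics with at least one GP each, 25% GP dropout, a baseline to follow-up correlation of 0.3 and two-sided alpha of 0.05, and states power above 80%.
- Economic evaluation: one result will be "cost per point improvement in concordance with the Guideline".

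The Primary analysis section uses a different label and leaves the model open: "primary outcome (proportion of guideline concordance) will be intention to treat using multilevel regression models (linear or Poisson regression, as appropriate". It has time-point and intervention status as fixed effects and lists three covariates, all stratification factors: state, clinic size and location. The adjusted-analyses paragraph under Secondary analysis describes the same main analysis, but its list ends "location (urban vs regional/rural), additional mental health training", which adds a fourth covariate.

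**The concern.** No section says how a proportion is formed from the score or what its denominator would be. The two permitted models also answer different questions. A linear model estimates a difference in points, the quantity the trial was sized on. A Poisson model with its usual log link estimates a ratio, which cannot be set against the 1.2-point target without knowing the mean score.

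Poisson is also a doubtful choice for this outcome. The score has a ceiling of 9, and the Poisson variance is tied to the mean, whereas the plan supplies its own variance. If the two disagree, the usual Poisson standard error is wrong and the test does not hold its nominal 5% level.

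The covariate conflict is a smaller matter of the same kind: two sections imply two different adjusted estimates for one primary analysis.

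**Working it through.** **Inputs.** From Sample size: difference 1.2, SD 1.75, correlation 0.3, two-sided alpha 0.05, 86 clinics, 25% dropout. GPs remaining: 86 × 0.75 = 64.5, taken as 64, or 32 per arm. Equal allocation is assumed from the 224/224 patient split. The standardised effect is 1.2/1.75 = 0.686, which matches the stated 0.69.

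**Step 1: reproduce the stated power.** With 32 per arm, SE = SD × √(2/32) = SD × 0.25, and power = Φ(1.2/SE − 1.96).

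| Linear analysis | SD used | SE | 1.2/SE | Power |
|---|---|---|---|---|
| Baseline-adjusted | 1.75 × √(1 − 0.3²) = 1.669 | 0.417 | 2.875 | 82.0% |
| Follow-up score only | 1.75 | 0.4375 | 2.743 | 78.3% |
| Change score | 1.75 × √(2 × 0.7) = 2.071 | 0.518 | 2.318 | 64.0% |

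Of these three, only the baseline-adjusted mean difference passes 80% (80.8% using the noncentral t). It needs 31 per arm, and 62/0.75 rounds up to 83, which is within 86.

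**Step 2: what 1.2 points becomes as a ratio.** The ratio is (m + 1.2)/m for control mean m: 1.60 at 2, 1.39 at 3.06, 1.30 at 4, 1.20 at 6. One target in points corresponds to many ratios.

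**Step 3: Poisson standard errors.** The planned variance is 1.75² = 3.0625. Under the null with mean m in both arms and follow-up scores only, the log ratio has model-based variance 2/(32m) and true variance 2 × 3.0625/(32m²). The ratio of model to true SE is therefore √(m/3.0625), and true alpha is 2 × [1 − Φ(1.96 × ratio)]. The mean score is not in the article, so a range is assumed.

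| Assumed mean | SE ratio | True alpha |
|---|---|---|
| 2 | 0.81 | 0.113 |
| 3.06 | 1.00 | 0.050 |
| 4 | 1.14 | 0.025 |
| 6 | 1.40 | 0.006 |

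Below a mean of about 3 the test is too liberal; above it, too conservative.

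**Step 4: simulation check.** Integer scores were clipped to 0–9, with 32 per arm, follow-up only and 1,500 runs per setting. Poisson rejection under the null was 0.067, 0.048, 0.022 and 0.005 at means 2, 3, 4.5 and 6. The direction agrees with the formula, with milder inflation at mean 2. Robust standard errors brought rejection to 0.049–0.062. At a control mean of 4.5, power for 1.2 points was 58% for Poisson, 77% for linear and 78% for robust Poisson.

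**Step 5: covariates.** Primary analysis lists state, clinic size and location. The adjusted-analyses paragraph says the main analysis adjusts for these, and its list also contains additional mental health training. Both cannot describe one model.

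**The case against.** The strongest reply is that the harm is possible rather than planned. Linear regression is permitted and named first, and a linear model on score/9 gives the same test as one on the score. The mean is not stated, and near a mean of 3 the Poisson standard error is correct. Robust variance removes the error elsewhere. A cluster random effect could absorb over-dispersion below a mean of 3, though not the under-dispersion above it. All of this stands, and it limits the standard-error point to a conditional one.

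It can also be said that a condensed article leaves model detail to an analysis plan that is not shown. That would excuse silence. It does not excuse one outcome carrying two descriptions, or an explicit choice between two effect measures.

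Three stronger readings are tempting but unsupported.

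- A reader might infer that the investigators will pick the model after seeing the data. The article says neither when nor on what basis the choice is made.
- A reader might infer that a Poisson analysis could not supply the cost-per-point result. It could: predicted arm means from a log-link model give a difference in points, and the article does not say the economic evaluation must use the regression coefficient.
- A reader might take the word proportion to mean that score/9 will go into a Poisson model with no offset, where the test would almost never reject. Nothing in the article says so.

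**Conclusion.** The inconsistency is real and lies in the text. The outcome is a 0–9 score in three sections and a proportion in the fourth, the primary effect measure is open between points and a ratio, and the two covariate lists for the main analysis differ. The stated power belongs to a linear, baseline-adjusted difference in points (82.0%).

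It would be too strong to say that Poisson necessarily gives wrong standard errors or can only cost power. The documents support only that it can be wrong in either direction: true alpha of about 0.11 at a mean of 2, falling to about 0.006 at 6, and correct near 3. Those figures assume a planning SD of 1.75 in both arms, 32 GPs per arm, follow-up scores only, no cluster effect and model-based variance. The pilot covered three dissimilar groups. If its SD pools them, the within-group SD is smaller and Poisson would be more conservative than shown. Robust variance settles the standard error, but the change of effect measure remains.

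**What to change.** In Primary analysis:

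- Name the 0–9 score as the primary outcome and drop the word proportion.
- Name the adjusted mean difference in points at 9 months, from a linear mixed model, as the primary result.
- Delete the Poisson option, or keep it only as a sensitivity analysis with robust variance.
- Give one covariate list in both sections: the three stratification factors, with additional mental health training moved to a sensitivity analysis.
- Use baseline once, either as a repeated outcome or as a covariate for the 9-month score. Time-point is already a fixed effect, so adding baseline as a covariate while it stays in the outcome vector would use it twice. If it stays as a repeated outcome, give both arms a common baseline mean; otherwise the contrast is in effect the change-score comparison, with 64.0% power.

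A scenario effect, reflecting that each GP sees three of eighteen scenarios, is an optional refinement; no size is claimed for its gain. The cost is wording only, with no change to data collection or sample size.

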## Methods

### Design

Implementing work-related Mental health conditions in general PRacticE (IMPRovE) is a hybrid III parallel cluster randomised controlled trial (RCT) of a complex intervention that involves receipt of academic detailing, enrolment onto a digital community of practice, and access to a library of resources to support guideline implementation. GP clinics (clusters) will be randomised to either intervention or control. A cluster design was chosen to avoid confounding that could arise if participating GPs from a single clinic were allocated to different arms of the trial. Participating GPs in clinics assigned to the intervention arm will receive the intervention. GPs in the control arm will not receive the intervention. Patients will be recruited to each arm (Figure 2).

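### The clinic random effect is left conditional in a trial that randomises clinics; the inflation of type I error is modest but avoidable, and it falls mainly on the patient outcomes

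*Protocol article*

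**What the plan says.** Under Design, the protocol article states that "GP clinics (clusters) will be randomised to either intervention or control". It gives the reason: "A cluster design was chosen to avoid confounding that could arise if participating GPs from a single clinic were allocated to different arms". More than one GP per clinic is therefore foreseen.

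Under Primary analysis, the primary outcome is to be analysed with "multilevel regression models (linear or Poisson regression, as appropriate), with time-point and intervention status as fixed effects". The next sentence reads "Clusters will be examined as a random effect for inclusion into the model". No rule for the examination is given. No other way of allowing for clustering, such as robust standard errors or a cluster-level analysis, is named.

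Under Secondary analysis, the patient outcomes are analysed "Using a similar mixed model approach as in the main analyses", so the conditional wording carries over to them.

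Under Sample size, the patient calculation does allow for clustering: "Calculations assume an alpha of 0.01, ICC of 0.03, and correlation of 0.5 between individual scores", with 7 to 24 patients per cluster. The primary calculation takes at least one GP in each of 86 clinics and states no ICC.

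**The concern.** When clinics are randomised, correlation within clinics is a consequence of the design. Whether to allow for it is not a question for the trial data to settle. The sentence leaves that decision until after the data are seen, and the decision changes standard errors and p-values. If the term is dropped while patients in a clinic are correlated, standard errors for the arm comparison are too small and the type I error exceeds its nominal level. For the patient outcomes, the plan expects such correlation when it sizes the trial and then permits the analysis to ignore it.

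**Working it through.** **Inputs from the protocol.** 86 clinics; 25% GP dropout; GP score difference 1.2, SD 1.75, baseline to follow-up correlation 0.3, two-sided alpha 0.05. Patients: 448 in all (224 per arm), 7 per clinic, so 448/7 = 64 clinics; cap 24 per clinic; ICC 0.03; alpha 0.01; d = 0.5.

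**The plan's own figures first.**
- Primary: 86 × 0.75 = 64.5, taken as 64 GPs, 32 per arm. If the 0.3 correlation is used for baseline adjustment, the SD is 1.75 × √(1 − 0.3²) = 1.669. Then 1.2 / (1.669 × √(2/32)) = 2.88; 2.88 − 1.96 = 0.92; power is 82.0%. This agrees with the claim that the sample "has >80% power to detect a medium-large effect size of Cohen’s d of 0.69".
- Patients: design effect DE = 1 + (7 − 1) × 0.03 = 1.18. Then 0.5 / √(2 × 1.18/224) = 4.87; 4.87 − 2.576 = 2.30; power is 98.9%, which satisfies the stated 90%.

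**Patient outcomes, clinic term left out.** With DE = 1 + (m − 1) × ICC, the reported standard error is 1/√DE of its correct size, and the actual two-sided type I error is 2 × [1 − Φ(z/√DE)].

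| Patients per clinic | DE | SE as share of correct | Error at nominal 1% | Error at nominal 5% |
|---|---|---|---|---|
| 7 (planned) | 1.18 | 92% | 1.8% | 7.1% |
| 24 (cap, every clinic) | 1.69 | 77% | 4.8% | 13.2% |

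**Patient outcomes, clinic term kept only if a 5% F-test is significant.** The test is an assumption. Simulated with 32 clinics per arm and ICC 0.03:

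| Patients per clinic | Term kept | Overall error at nominal 1% | Overall error at nominal 5% |
|---|---|---|---|
| 7 | 28% | 1.4% | about 6% |
| 24 | 92% | 1.2% | 5.3% |

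With the term always included, simulated error stays nominal (about 1% and 5%).

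**GP outcome, several GPs per clinic.** The protocol gives no ICC here, so 0.03 to 0.30 is an assumed range. With the term left out at nominal 5%:
- 1 GP per clinic: DE = 1, error 5.0%.
- 2 GPs: DE 1.03 to 1.30, error 5.3% to 8.6%.
- 3 GPs: DE 1.06 to 1.60, error 5.7% to 12.1%.

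Under the same assumed 5% test, with 2 or 3 GPs per clinic and ICC 0.05 to 0.30, overall error is 5.2% to 6.0%.

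**GP outcome, one GP per clinic.** The clinic intercept is then also the GP intercept. Suppose it is dropped and nothing else in the model links a GP's two visits (correlation 0.3):
- For a difference in change, the true variance is 1 − 0.3 = 0.7 of what the model assumes. The standard error is too large by 1/√0.7 = 1.20, and error is 2 × [1 − Φ(1.96/√0.7)] = 1.9%, which is conservative.
- For an arm effect averaged over both visits, the ratio is 1 + 0.3 = 1.3, and error is 2 × [1 − Φ(1.96/√1.3)] = 8.6%.

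**The case against.** The strongest reply is that the model is already called multilevel, and the patient analysis a mixed model, so at least one random level is intended. A GP or patient level for repeated visits, with clinic examined as an additional level, is a compatible reading. This stands in part: it cannot be established that a GP's two visits would be treated as independent, so the 1.9% and 8.6% figures are conditional. It does not settle the clinic term, because a GP or patient level does not capture correlation between different people in the same clinic.

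A second reply is that the harm is small, and this largely stands. A reader might infer that the check will usually discard the clinic effect and that error could reach 13.2%. The two do not go together. At 7 per clinic a 5% test would often drop the term, but dropping it then costs little. At 24 per clinic dropping it would cost much, but the test keeps it in about 92% of trials. The 13.2% also needs every clinic at the cap, whereas the plan counts on 7, and it is stated at the 5% level when the patient outcomes are planned at 1%.

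A reader might also infer that the primary GP result will have standard errors that are too small. The protocol does not support that for its base case of one GP per clinic, where there is no between-GP clustering to ignore and a change contrast would be conservative.

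Finally, full random-effects detail is commonly left to an analysis plan. That would excuse silence. Here the article states a rule, and the rule makes the effect of the randomised unit optional.

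**Conclusion.** The sentence is wrong as written and should be fixed; it does not undermine the trial. The size depends on how inclusion is decided, which the protocol does not say. For patient outcomes at the planned 7 per clinic, error at nominal 1% is between about 1.4% (5% test) and 1.8% (term always left out). These figures rest on the protocol's ICC of 0.03, equal cluster sizes and a comparison at a single time point. For the GP outcome, inflation from clinic clustering needs clinics with more than one GP and an ICC that the protocol does not state. The planned primary power is unaffected with one GP per clinic, where the design effect is 1.

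**What to change.** Replace the sentence under Primary analysis with:

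> Clinic will be included as a random effect in all GP and patient models, whatever its estimated variance or p-value. Correlation between repeated visits of the same GP or patient will also be modelled (for GPs, by a separate GP-level term only where clinics contribute more than one GP, since with one GP per clinic the clinic intercept serves this purpose).

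The bracketed condition matters: with one GP per clinic, a clinic intercept and a GP intercept cannot be estimated separately, so requiring both throughout would not work.

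The cost is this one change of wording and slightly wider intervals in some analyses. No change to the sample size follows from it.

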#### Secondary analysis

*Patient analyses*: Using a similar mixed model approach as in the main analyses, changes in patient health status (using the SF-36 v2), and work participation (using relevant measures of the National Return To Work Survey) will be measured by comparing the scores on patient surveys from baseline to 3, 6, and 9 months following their initial GP consultation.

*Adjusted analyses*: The main analysis and subgroup analyses above include adjustment for the stratification factors, which are state, clinic size (GP equivalent full time >5 (yes/no)), and location (urban vs regional/rural), additional mental health training.

*Missing data*: As the GP and patient-level data are longitudinal samples, a missing data analysis will be done on each longitudinal data set and investigations made for predictors of missingness. These investigations will examine the effect of key demographic and other factors particularly on the presence of missing outcomes. If outcome data is found to not be missing at random, then multiple imputation will be applied using the predictors for missingness.

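### The missing-data rule is triggered by data not missing at random, which observed predictors cannot show and which imputation from those predictors does not correct

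*Protocol article*

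**What the plan says.** The missing-data paragraph of the protocol article (Statistical methods, Secondary analysis) has three steps.

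- Scope: "a missing data analysis will be done on each longitudinal data set and investigations made for predictors of missingness". The data sets are the GP data, which carry the primary outcome, and the patient data.
- Diagnostic: "These investigations will examine the effect of key demographic and other factors particularly on the presence of missing outcomes".
- Decision rule: "If outcome data is found to not be missing at random, then multiple imputation will be applied using the predictors for missingness".

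The main analysis (Primary analysis) "will be intention to treat using multilevel regression models (linear or Poisson regression, as appropriate), with time-point and intervention status as fixed effects". Its covariates are state, clinic size and location, and clusters are considered as a random effect. The adjusted-analyses paragraph adds mental health training.

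The Sample size section allows for substantial loss: "A sample size of 86 clinics (clusters), with a minimum of one GP per cluster and assuming a GP dropout rate of 25" per cent. The Blinding section accepts that GPs will come to know their arm.

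**The concern.** The decision rule joins a condition to a method that does not fit it.

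The trigger cannot be reached by the diagnostic. Whether data are missing at random or not depends on the scores that were not seen. An association between observed factors and missingness rules out missing completely at random and goes no further.

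The remedy does not answer the trigger either. Imputing from observed predictors assumes that, given those predictors, lost and retained GPs have the same score distribution. That is the missing-at-random assumption.

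Read literally, the rule also leaves a gap on the other side. If loss depends on an observed factor outside the model, the data are missing at random given that factor. Imputation would help there, but the rule does not call for it.

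The primary comparison is at stake. About a quarter of GPs may have no 9-month score. The outcome requires a GP who knows the allocation to complete three scenarios of about 15 minutes each. Loss related to engagement or concordance is plausible, and the paragraph assigns that case a method that cannot deal with it.

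**Working it through.** **Amount of missing data.** 86 × 0.75 = 64.5 GPs at one per clinic, so about 64, or 32 per arm. The patient figures agree: 448 / 7 = 64 clinics.

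**The plan's own figure.** The Sample size section claims that the design "has >80% power to detect a medium-large effect size of Cohen’s d of 0.69". Its inputs are a 1.2-point difference and an SD of 1.75, so d = 1.2 / 1.75 = 0.69. With the stated baseline correlation of 0.3, the baseline-adjusted SD is 1.75 × √(1 − 0.3²) = 1.67. With 32 per arm and two-sided alpha 0.05, power is 82.0%. The claim reproduces, and no stated figure is in dispute.

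**Does imputation from observed predictors fix the named condition?** A large-sample simulation (2,000,000 GPs, no clustering) used a true effect of 1.2, SD 1.75, baseline correlation 0.3 and 25% of 9-month scores missing overall. These inputs were assumed: an additional observed predictor x correlated 0.4 with the outcome, and missingness changing by 0.5 or 1.0 log-odds per SD of the variable that drives it. The observed-data analysis regresses the 9-month score on arm and baseline. The imputation works by arm from baseline and x, followed by the same regression. Each cell gives the estimates at 0.5 and 1.0.

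| Missingness depends on | Observed data | After imputation |
|---|---|---|
| Baseline score (at random) | 1.20, 1.20 | 1.20, 1.20 |
| x, opposite directions by arm (at random given x) | 1.37, 1.50 | 1.20, 1.20 |
| Own 9-month score, low scorers lost, intervention arm only (not at random) | 1.40, 1.56 | 1.36, 1.51 |
| Own 9-month score, low scorers lost, both arms (not at random) | 1.15, 1.06 | 1.16, 1.08 |

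Share of the bias left after imputation when data are not missing at random:

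- Intervention arm only: (1.362 − 1.200) / (1.396 − 1.200) = 0.162 / 0.196 = 83%, and (1.507 − 1.200) / (1.564 − 1.200) = 0.307 / 0.364 = 84%.
- Both arms: (1.200 − 1.161) / (1.200 − 1.153) = 0.039 / 0.047 = 83%, and (1.200 − 1.084) / (1.200 − 1.064) = 0.116 / 0.136 = 85%.

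The method works in the second row, for which the literal rule does not call for it. It mostly fails in the last two rows, which are the rule's stated trigger.

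**Possible size in this trial (assumed).** Let p be the fraction lost in an arm and D the amount by which lost GPs score below what observed predictors imply. The bias in the difference is p(intervention) × D(intervention) − p(control) × D(control).

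- Intervention arm only, p = 0.25, D = 0.5 SD = 0.875: 0.25 × 0.875 = 0.22 points; 0.22 / 1.2 = 18%.
- Intervention arm only, p = 0.25, D = 1.0 SD = 1.75: 0.25 × 1.75 = 0.44 points; 0.44 / 1.2 = 36%.
- Equal p and D in both arms: the terms cancel.
- More loss in the control arm, because its scores are lower: the bias is towards zero. In the last row of the table at 1.0 log-odds per SD, 30.4% of controls and 19.6% of intervention GPs were lost.

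**The case against.** The strongest reply is that the sentence has only lost the word 'completely'. The one diagnostic described is a search for observed predictors of missingness. In practice the rule can fire only when such predictors exist, and imputation then uses them. That is an ordinary missing-at-random procedure, and the second row of the table shows it working. This stands as to likely intent. A reader might infer that the rule is simply backwards and prescribes imputation only where it fails; as it would be carried out, that is not so.

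Nor is the main analysis unsound. A likelihood fit of the planned multilevel model to all available scores, linking each GP's baseline and 9-month values, is valid under missing at random given its terms. The first row of the table shows no need for imputation in that case. This stands too.

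It can also be said that delta-adjusted analyses usually belong in a statistical analysis plan, which is not shown. That is fair: their absence from a journal article is not a fault in itself. The fault is that the article names the not-at-random condition and assigns it a method that does not address it.

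Finally, the 18% to 36% rests on an assumed departure in one arm. It is defined as lying beyond observed prediction, so imputation cannot remove it by construction. This stands, and the figure is an illustration only.

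**Conclusion.** The sentence is wrong as written and governs the primary outcome. Its trigger cannot be established from observed data, and its remedy assumes the trigger is false. Both points follow from the definitions and do not depend on the simulation, whose mechanisms and strengths are assumed.

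The size and direction of bias in this trial are unknown. The illustration runs from an overstatement of 0.22 to 0.44 points, if only the intervention arm is affected, to no bias or bias towards zero if both arms are. A reader might infer that the intervention effect will be inflated. The documents do not support that: the 25% is an overall planning allowance, and nothing indicates that loss will differ by arm. They also do not say that an imputed result will be reported as having dealt with non-random dropout, though the present wording would allow it.

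Sample size, power and main model are unaffected. This is a should-fix point.

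**What to change.** Replace the decision rule, in an amendment or in the statistical analysis plan before outcome data by arm are examined, with three statements:

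1. The multilevel model, fitted to all available GP and patient data, assumes that outcomes are missing at random given the terms in the model.
2. If observed factors predict missing outcomes (data not missing completely at random), they enter as covariates or through multilevel multiple imputation under that same assumption.
3. Whatever the diagnostics show, a sensitivity analysis for data not missing at random is run on the 9-month concordance score. It uses delta-adjusted or tipping-point imputation, with shifts varied separately by arm (for example from 0 to −1.2 points, the size of the target difference), and reports the shift at which the conclusion would change. The same approach can be used for the patient outcomes.

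The cost is a few lines of wording and a small extra analysis. No additional data or participants are needed.
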